**Infusion related toxicities (IRTs)**

- Infusion related events would be monitored for approximately 6 hours following the initiation of infusion.
- Following criteria will be carefully evaluated and recorded on all days starting from Day 1 till last day of IP administration as per NCI-CTC AE version 3:
- Fever (rise in oral temperature>1°C above baseline)
- Chills and rigor
- Nausea, vomiting
- Dyspnoea
- Hypotension/hypertension
- Tachycardia

**Other AEs**

Other AEs would be appropriately graded based on the NCI-CTC-AE-v3 criteria. These would be statistically analyzed to know the safety of Amphotericin B emulsion compared to AmBisome along with the following categories -

- Incidence of AEs by preferred term (used from MedDRA)
- Incidence of AEs by system organ class
- Incidence of related/unrelated AEs
- AEs irrespective of causality
- Number of patients experiencing an AE at least once
- Display of severe AEs

**Events NOT to be reported as AEs**

- Progression of underlying disease/study indication/lack of efficacy of the IP should NOT be reported as an AE/SAE.

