**Safety Data from previous clinical studies with Amphomul^®^**

More commonly encountered side effects:

Chills, fever, headache, nausea and vomiting, loss of Appetite, diarrhoea, stomach pain, hypokalemia, hypoxia.

Less commonly encountered side effects:

Anaemia, leucopoenia, renal function impairment, respiratory distress, thrombocytopenia, back pain, chest pain, dark urine, jaundice, skin rash, anaphylactic reaction, dyspnoea, hypertension, hypotension, tachycardia, facial edema, hives, itching, skin redness, unusual tiredness, weakness.

The association of the above adverse reactions with AMB emulsion is uncertain.

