## Definitions

### Adverse Events

An AE is any untoward medical occurrence in a patient administered a pharmaceutical product and which does not necessarily have a causal relationship with the treatment. An AE may be any unfavorable symptom, sign, syndrome or disease or even a clinically significant abnormal laboratory value, which occurs for the first time during the course of a study having been absent at baseline or, if present, worsens from baseline, regardless of the suspected cause of the event.

Additionally, they may include signs/symptoms resulting from drug overdose, drug withdrawal, drug abuse, drug misuse, drug interactions, and drug dependence.

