### Serious Adverse Events

An AE will be labeled to be SAE if it-

- Results in death
- Is life threatening
- Requires in patient hospitalization
- Prolongs existing hospitalization
- Results in persistent or significant disability/incapacity
- Is a congenital anomaly/birth defect
- Amounts to any ‘other significant clinical/laboratory event’ of major concern in the opinion of the Investigator

Examples of ‘other significant medical events’ that should be considered serious for the purposes of this study include, but are not limited to, severe early onset reaction such as anaphylaxis, vasovagal episodes, episodes of hypotonia, hyporeactivity or hyperventilation, convulsions etc.

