### Assessment of Causality

Every effort should be made by the PI to explain each AE and assess its causal relationship, if any, to administration of the study drug.

All expected reactions would be considered related to study drug administration.

Causality of all other AEs should be assessed by the PI depending upon various factors like the temporal relationship of the AE to study drug administration, whether AE follows a known pattern of response to IP, any other cause to which the AE can be attributed or intensity of AE changes on rechallenge or dechallenge.

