## Reporting of SAEs

- Any SAE occurring during the course of the study should be treated by established standards of care to protect the life and health of the patient.
- If such treatment constitutes a significant deviation from the protocol, the Investigator should notify SIRO immediately to determine whether the patient should be dropped out from the study.
- Any SAE, irrespective of causality, must be **immediately** notified to the safety team at SIRO Clinpharm Pvt. Ltd. **by telephone ([contact], 24 hour*‑*contact - [name]).**
- This must be followed up **within 24 hours by facsimile *(+*[name]*)*** on the study specific SAE reporting form with as much detailed information regarding the event that is available.
- Investigators should not wait to receive additional information to fully document the event, before notifying SIRO of a SAE.
- The SAE reporting form should detail all relevant aspects of the AEs in question. Where applicable, information from relevant hospital case records and autopsy reports should be obtained and provided, in a blinded fashion, to SIRO.
- All SAEs should be reported within 24 hours to SIRO and, within 7 calendar days to IRB/IEC on Investigator’s knowledge of the event. Confirmation of submission to the IRB/IEC must be forwarded to SIRO.
- The event must also be recorded on the CRF AE page.

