## Protocol Specific safety issues

- All AEs during the study will be graded as per NCI-CTC-AE‑v3.
- Laboratory investigations pertaining to safety analysis (hematological, biochemical and serological and urinalysis*)* will be done from screening visit onwards after starting treatment with Amphomul^®^ as mentioned in Section 14. Study Calendar.
- The evaluating parameters of safety criteria are:
  - Physical findings such as body temperature, weight, rigors/chills, nausea, vomiting, dyspnoea, hypotension, hypertension, tachycardia and any other significant clinical finding.
  - Laboratory parameters as mentioned above.
- The safety criteria shall be evaluated with the definition of change in the laboratory parameters.
- All AEs will be carefully evaluated, recorded, and reported throughout the study.

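### Section 18.6 excludes disease progression and lack of efficacy from AE/SAE reporting without limit, so a fatal or serious event attributed to kala-azar can leave the SAE record

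*Protocol*

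**What the plan says.** The Protocol's safety rules that bear on this point are:

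- **Section 18.6, events not to be reported as AEs:** "Progression of underlying disease/study indication/lack of efficacy of the IP should NOT be reported as an AE/SAE". Nothing is added about fatal or otherwise serious cases, and progression is not defined.
- **Section 18.1.1, AE definition:** an AE includes a finding that was absent at baseline or, "if present, worsens from baseline, regardless of the suspected cause of the event".
- **Section 18.1.3, SAE definition:** an AE is serious if, among other criteria, it "Results in death", is life threatening, or leads to or prolongs hospitalisation. No exemption is made for disease-related outcomes.
- **Section 18.4, SAE reporting:** "Any SAE, irrespective of causality, must be" notified at once to the CRO's safety team, and all SAEs also go to the ethics committee.
- **Section 18.6, general part:** "All AEs will be carefully evaluated, recorded, and reported throughout the study". The same section plans an AE summary that ignores causality.
- **Section 20.2.3, safety analysis:** the proportions of patients with AEs and SAEs are tabulated on the treated population, and SAE reports are presented one by one.

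**The concern.** The comparative safety of the two products is the secondary objective (10.1.2), and its SAE component comes from what sites report. One rule makes the reporting of a serious event independent of its cause. Another removes the event when its cause is judged to be the disease. The trial is open label (15.3), so that judgement is made by someone who knows the arm. If serious events are called progression more readily in one arm than in the other, the SAE comparison is distorted, and the sponsor, regulator and ethics committees do not receive those events through the SAE route.

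**Working it through.** The protocol states no figure on this point, so the check sets the rules side by side and traces what still captures an affected event.

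**Step 1. Do the rules conflict?** Take a patient who worsens after infusion and dies, where the investigator attributes the death to kala-azar.

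| Rule | Result for this patient |
|---|---|
| 18.1.1 AE definition | AE, since cause is irrelevant |
| 18.1.3 seriousness | SAE, since the outcome is death |
| 18.4 SAE reporting | Must be notified |
| 18.3.3, Table 5 | An AE that receives a causality grade |
| 18.6 exclusion | Neither AE nor SAE |

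The first four agree and the fifth contradicts them. Table 5 already provides for events explained by the patient's clinical state. They are graded Unrelated or Unlikely or, if the timing is reasonable and the clinical state is only an alternative explanation, Possible, which counts as related. The same event can therefore be a related AE under Table 5 and no event under 18.6.

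**Step 2. Does the protocol limit exclusions elsewhere?** Yes. Section 18.7 says that pregnancy is not an AE or SAE, then lists the outcomes for which it becomes one. Section 18.6 contains no such list.

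**Step 3. What does the serious event lose?**

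- SAE proportions and individual SAE reports (20.2.3): lost.
- Notification to the CRO and the ethics committee (18.4): lost.
- Six-monthly SAE listing (18.5): lost.
- Expedited report (18.5): lost where Table 5 would have graded the event at least Possible and the event is unexpected.

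**Step 4. What remains?** Death is a listed withdrawal reason (12.6.1), and the date and reason go into the CRF (12.6.3). No safety table of deaths is described. The efficacy side is not a reliable substitute, because the failure conditions in 17.2 are amastigotes on smear and discontinuation for intolerance; death is not named.

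**Step 5. What happens to cytopenias?** Haematology is drawn at screening, Day 7, Day 30 and 6 months (study calendar). Laboratory values are a secondary endpoint of their own (10.2.2) and are summarised whatever the AE coding (20.2.3). The DLT definition in Section 13 requires drug-relatedness in criteria i and ii. The haematological criteria iii (a fall of at least 33% from a grade III or IV baseline) and iv (a drop to grade IV from a better baseline) do not carry that condition and apply up to Day 7. A cytopenia called progression can therefore lose its AE/SAE entry, mainly after Day 7, but not its place in the laboratory summaries.

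**Step 6. How much does one event count?** Planned enrolment is 375 and 125 (11.2). If all are treated, one unreported event changes the SAE proportion by 1/125 = 0.80 percentage points in the AmBisome arm and by 1/375 = 0.27 in the Amphomul arm. This shows the weight of a single event; it does not estimate how many there will be.

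**The case against.** The strongest reply is that 18.6 is a deliberate, specific exception to a general definition. It has its own heading, and the rules in 18.1.3 and 18.4 apply only to events that are already AEs. Failure and relapse are captured as efficacy outcomes by fixed splenic scores (Section 17), and slides of 10% of patients are checked at an independent laboratory (Section 19). Keeping those outcomes out of the AE counts is legitimate.

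That part stands: excluding an efficacy finding as such is not an error. It does not settle the serious case. No text says that the exception overrides the cause-independent SAE rule. Smear criteria govern treatment failure, not whether a clinical deterioration is called progression.

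Several stronger readings are tempting, and the document does not support them:

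- **That cytopenias leave the safety comparison.** They do not; the laboratory summaries and, up to Day 7, the haematological DLT criteria keep them.
- **That the same fall in haemoglobin is either automatically drug related or no event at all.** Section 9.5 lists "Anaemia, leucopoenia, renal function impairment, respiratory distress, thrombocytopenia" among less common side effects, and 18.3.3 says "All expected reactions would be considered related to study drug administration". But 18.1.4 defines unexpected events against the Investigator's Brochure, which is not at hand, and 9.5 itself calls the association with the emulsion uncertain. This gives no basis for asking that 18.3.3 be rewritten.
- **That many such deaths should be expected.** The mortality of nearly 100% in Section 9.1 is for untreated disease. Every patient who counts here is treated, and rescue medication is provided for.
- **That deaths are concealed.** They remain in the disposition data; what is lost is their standing as safety events.

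**Conclusion.** The point holds for serious events. The exclusion in 18.6 is unlimited and contradicts 18.1.1, 18.1.3 and 18.4. If sites follow it literally, a death, life-threatening event or hospitalisation attributed to kala-azar is absent from the SAE tabulation, individual SAE reports, notification and periodic listings, and from expedited reports where these would have applied. For cytopenias the loss is confined to the AE/SAE entry, mainly after Day 7.

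The size cannot be estimated, because the protocol gives no rate of disease-attributed serious events and no way to know how often investigators would use the exclusion. The conclusion rests on two assumptions: that 18.6 is applied as worded, and that at least some serious events are judged to be progression. It does not assume that attribution will differ by arm, only that the open-label design allows it.

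**What to change.** Reconcile the sections by wording:

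1. Limit the exclusion in 18.6 to the efficacy finding itself: a positive splenic score or a relapse, without more, is recorded as an efficacy outcome and not as an AE.
2. State in 18.6 that any event meeting a seriousness criterion of 18.1.3 is reported as an SAE under 18.4 whatever its suspected cause, including progression or lack of efficacy.
3. State that causality of these events is assessed by Table 5 in both arms.

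There is no need to require an AE for every graded worsening; that would largely cancel a legitimate exception. The cost is a change of protocol text and some additional SAE forms. Design, sample size and visit schedule are unaffected.

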## Exposure *in utero*

- **Pregnancy during a clinical trial is required to be reported for:**
  - - Female patients exposed to an IP or
    - Partners of male patients participating in the study
  - In event of a pregnancy during the study, the same is required to be reported to the SIRO safety team **immediately via telephone** and in the form of **Pregnancy Report Form (PRF) within 24 hours from the knowledge** of the investigator about the pregnancy.

**A Pregnancy Outcome form** **(POF)** will then be sent to the site from SIRO, which should be filed and a copy of which will be faxed back to the SIRO safety team **within 24 hours** from the knowledge of the pregnancy reaching its outcome.

- - Pregnancy during a clinical trial itself is **not regarded as an AE/ SAE unless**
    - There is a suspicion that an IP may have interfered with the effectiveness of a contraceptive medication.
    - The concerned pregnancy results in one of the following outcomes:

1. Miscarriage/late spontaneous abortion
2. Stillbirth
3. Congenital Malformation/Anomaly
4. Neonatal death *(*within 28 days from birth)
5. Infant death *(*after 28 days from birth but assessed as related to the IP by the Investigator)
   - In case for any pregnancy reported during a clinical trial, if the IP is suspected to have interfered with the effectiveness of a contraceptive medication and/or results in one of the above outcomes, the investigator is required to fill the AE form and the corresponding SAE form patient to the same timelines as mentioned above.

# 19. BLOOD/TISSUE SAMPLE HANDLING AND ANALYSIS

**Laboratory assays**

- Approximately 10 mL of blood will be taken by venous puncture on the days specified in the study calendar. It will be appropriately divided and transferred to respective containers meant for biochemical, microbiological and serological investigations, as stated in the protocol.
- Splenic aspirate
  - Splenic aspirate smear examination (with grading of parasite density) will be performed before initiating treatment with the study drug. However, the test will not be repeated if, Kala-azar has been diagnosed before starting the IP, either by splenic aspirate or bone marrow aspirate smear by the same laboratory (which will be used in this study) and has not been followed by any therapy.
  - Prothrombin time will have to be carried out before splenic aspiration and procedure will be done only if the result is ≤ 4 seconds above the control.
  - Splenic aspirate slides will be stained by either Leishman’s stain or Giemsa stain. Both the stains contain eosin as Acidophilic Dye Component. Leishman’s stain contains Methylene Blue as Basophilic Dye Component whereas Giemsa Stain contains azure B as Basophilic Dye Component.  Leishman's Stain is technically easy to perform and procedure of staining takes less time. Parasite density will be graded microscopically (X10 eyepiece X100 objective) using a logarithmic scale from +1 (1 to 10 amastigotes per 1000 oil immersion microscopic fields) to +6 (>100 amastigotes per oil immersion field).
    - Timings of laboratory investigations would be as mentioned in Section 14 Study Calendar.
    - Any additional/unscheduled investigation can be done at the investigator’s discretion as needed.
    - These investigations, as deemed necessary will also be repeated on the EOS Visit.
    - All blood and body fluids/ tissue samples will be analyzed by the concerned local laboratory.
    - Quality control of slides of 10% of patients will be done at independent laboratory. (at screening as well as initial cure)
    - Window periods of ±5 days will be acceptable for the investigations being done at Day 30 and Day 45. Window period of -2 weeks to +4 weeks will be accepted for investigations being done at the EOS visit.
    - If blood samples from the patients are not drawn at the protocol-defined intervals, and in accordance with the methodology set in this protocol, the patient will not be considered as protocol compliant. However, given the study indication and underlying disease, this will not be reported as deviation of the protocol.

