**Efficacy Criteria**:

- Initial cure (splenic aspirate score 0 on Day 30 or on Day 45)
- Clinical improvement on Day 30 after study drug administration
  - Absence of fever; and >1 out of following:
    - Increase in hemoglobin concentration by >10% compared to baseline
    - Any weight gain compared to the baseline visit
    - Decrease in spleen size by >33% from baseline
- Definitive cure:

1. Initial cure at Day 30 or Day 45
2. No clinical signs and symptoms of relapse of Kala-azar for 6 months after study drug administration. If clinical signs and symptoms of relapse of the disease is suspected at any time during the 6 month follow up, splenic aspirate shall be performed at 6 months or earlier after study drug administration.

Proportion of patients achieving all three-efficacy endpoints will be compared across the two groups.

**Safety criteria:** Safety assessments will be done on Day 7 and Day 30. Safety will be assessed by the following parameters.

1. Number of AEs and SAEs
2. Incidence of IRTs
3. Incidence of nephrotoxicity and hepatotoxicity
4. Laboratory values for different parameters

All AEs, SAEs, changes in laboratory values, vital signs and physical condition will be monitored throughout the course of the study.

All tests will be performed at the local laboratory at each centre.

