  - Hematology:- hemoglobin, RBC, ESR, platelets, total and differential leukocyte count
  - Biochemistry:-
    - Liver function tests (Serum ALT, AST, alkaline phosphatase, total bilirubin, serum albumin, prothrombin time)
    - Renal function tests (serum creatinine, BUN*)*
    - Electrolytes (sodium, potassium, magnesium)
  - HIV test, HCV and HBsAg tests.
  - Fasting blood sugar test.
  - Parascreen antigen test for detection of malarial parasites
- X-ray chest and 12-lead ECG
- UPT (for females of child bearing potential only)
- Urine analysis (routine, microscopy )
- **Splenic aspirate**
  - Splenic aspirate will be performed to assess parasitological cure.
  - If the spleen is not palpable then Bone marrow aspirate will be done.
  - Splenic aspiration will be done only if rK39 test is positive.
  - Prothrombin time will have to be carried out before splenic aspiration and procedure will be done only if result is ≤4 seconds above the control.
  - Splenic aspirate slides will be stained by either Leishman’s stain or Giemsa stain. Both the stains contain eosin as Acidophilic Dye Component. Leishman’s stain contains Methylene Blue as Basophilic Dye Component whereas Giemsa Stain contains azure B as Basophilic Dye Component. Leishman's Stain is technically easy to perform and procedure of staining takes less time. Parasite density will be graded microscopically (X10 eyepiece X100 objective) using a logarithmic scale from +1 (1 to 10 amastigotes per 1000 oil immersion microscopic fields) to +6 (>100 amastigotes per oil immersion field). The grading will be done as follows:

| **Table 1: Grading system for grading parasite density microscopically** | |
| --- | --- |
| **Grade** | **Average parasite density** |
| +6 | >100 amastigotes/field |
| +5 | 10-100 amastigotes/field |
| +4 | 1-10 amastigotes/field |
| +3 | 1-10 amastigotes/10 fields |
| +2 | 1-10 amastigotes/100 fields |
| +1 | 1-10amastigotes/1000 fields |
| 0 | No amastigotes/1000 fields |

- Previous and concomitant medications will be recorded.
- Data obtained from the laboratory investigations will be used as soon as available to decide patient’s participation in the study.

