**Visit 3 - End of study visit- 6 months after study drug administration (-2 weeks to +4 weeks):**

- A thorough clinical examination will be done.
- Safety assessment (AEs, SAEs, IRTs, check for nephrotoxicity and hepatotoxicity and laboratory values for different parameters) will be done
  - Laboratory investigations will be done:-Hematology, Renal and Liver function tests, electrolytes as outlined in the screening section.
- Splenic aspirate will be done to assess parasitological cure in patients in whom a relapse of the illness is indicated by recurrence of fever, splenic enlargement. In others, only clinical assessment will be done to define definitive cure at 6 months.
- Prothrombin time will have to be carried out before splenic aspiration and procedure will be done only if result is ≤ 4 seconds above the control
- Definitive cure will be defined as initial cure at Day 30 or 45 followed by absence of clinical signs and symptoms of relapse of Kala-azar till 6 months after study drug administration. If clinical signs and symptoms of relapse of the disease is suspected at any time during the 6 month follow up, splenic aspirate shall be done at 6 months or earlier after study drug administration.
- Vital signs will be recorded.
- Monitoring, recording and reporting for AEs, if any, will be done appropriately
- Previous and concomitant medications will be recorded.

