## Randomization and Blinding

- Since this is an open label study, blinding is not applicable.
- Permuted Block randomization schedule with block of size 4 and ratio of 3:1 in the two groups (Amphomul and AmBisome) will be generated for each center.
- Treatment with IP/Comparator drug will begin only after successful screening (signing informed consent and fulfillment of all eligibility criteria).
- After meeting eligibility criteria, the patient will sequentially be allotted to unique subject ID and treatment as per randomization schedule for that center.
- A separate screening and enrolment log will be maintained.
- Neither the Investigators nor patient/patient’s LAR will be blinded to the treatment regimen.

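### Splenic smears that decide initial cure are read locally in an open-label trial, and the protocol does not keep the arm from the reader, so a required part of the primary endpoint is exposed to possible reader bias

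*Protocol*

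**What the plan says.** - **Masking.** Section 15.3 states that "Since this is an open label study, blinding is not applicable" and adds that "Neither the Investigators nor patient/patient’s LAR will be blinded to the treatment regimen". Smear readers are not mentioned, here or elsewhere.
- **Where smears are read.** Section 19: "All blood and body fluids/ tissue samples will be analyzed by the concerned local laboratory". The study summary agrees: "All tests will be performed at the local laboratory at each centre".
- **Independent check.** Section 19: "Quality control of slides of 10% of patients will be done at independent laboratory. (at screening as well as initial cure"). It does not say how patients are selected, whether the checking reader is masked, or whether that reading replaces the local one.
- **Threshold.** In Table 1 (Section 13), grade 0 is "No amastigotes/1000 fields" and grade +1 is 1 to 10 amastigotes in the same number of fields.
- **Consequence.** Under Sections 13 and 17, a Day 30 score of 0 is initial cure, +1 leads to a repeat aspirate at Day 45, and a higher score is treatment failure. At Day 45, 0 is initial cure and +1 or more is treatment failure.
- **Link to the primary analysis.** Definitive cure needs initial cure followed by "absence of clinical signs and symptoms of relapse of Kala-azar till 6 months after study drug administration". Section 20.2.2 tests the difference in definitive cure with a margin of -0.10 on the lower limit of a two-sided 95% confidence interval.

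**The concern.** Open-label dosing is a reason not to mask patients and investigators. It is no reason to leave the microscopist unmasked, since a slide can be coded whether or not the infusion was open. The protocol treats the two as one decision.

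The reading is a search for rare objects, and at the boundary a single doubtful object changes the grade. If the reader knows or can find out the arm, that call can lean one way. Section 15.3 allots the subject ID and the treatment together from the centre's schedule, so a slide labelled only with the subject ID can be linked to an arm by anyone with access to site records.

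At stake is the difference in definitive cure itself. Reading that favours Amphomul makes a false non-inferiority conclusion more likely; reading that favours AmBisome lowers power. The recorded scores alone cannot tell arm-dependent reading from a treatment effect.

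**Working it through.** No stated figure is in dispute; the arithmetic only shows what a small reading shift would mean on the trial's scale.

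**Inputs from the protocol (Sections 11.2 and 20.2.2).** 300 Amphomul and 100 AmBisome evaluable patients, margin 0.10, two-sided 95% interval, true difference 0, at least 80% power, 20% loss.

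**Assumed, because the protocol gives none.** The cure rate (85%, 90% or 95%) and the share of Amphomul patients whose outcome is changed by arm-aware reading (1%, 2% or 3%, that is 3, 6 or 9 of 300).

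**The plan's own figures.** 400 / (1 - 0.20) = 500 reproduces. The 400 cannot be checked without a cure rate. With unpooled variance, one-sided 0.025 and 80% power, the total is 412 at 89% and 396 at 89.5%, so 400 fits an assumed rate of about 89% to 89.5%.

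**Precision.** Half-width = 1.96 × sqrt(p(1 - p)(1/300 + 1/100)).

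| Common cure rate | Standard error | Half-width |
|---|---|---|
| 85% | 0.0412 | 8.1 points |
| 90% | 0.0346 | 6.8 points |
| 95% | 0.0252 | 4.9 points |

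**Effect of a shift s in the Amphomul arm.** If every affected patient ends as a definitive cure, the estimate moves by s: 1, 2 or 3 points, or 10%, 20% or 30% of the margin. This is the most it can be for that s. A patient misread as 0 at Day 30 who would have scored 0 at Day 45 is an initial cure either way, and one who later relapses fails definitive cure either way.

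**False non-inferiority at full pass-through.** Suppose Amphomul is truly 10 points worse, so its observed rate is pt = pr - 0.10 + s, where pr is the AmBisome rate. Then P(claim) = Φ(s / SE - 1.96), with SE = sqrt(pt(1 - pt)/300 + pr(1 - pr)/100). Example, pr = 0.90 and s = 0.01: SE = sqrt(0.81 × 0.19/300 + 0.90 × 0.10/100) = 0.0376, giving Φ(0.266 - 1.96) = 4.5%.

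| Shift | AmBisome 90% | AmBisome 95% |
|---|---|---|
| 0 | 2.5% | 2.5% |
| 1% | 4.5% | 5.2% |
| 2% | 7.7% | 10.1% |
| 3% | 12.5% | 18.0% |

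**Opposite direction.** With equal true rates of 90%, power is 82%. A shift of 1%, 2% or 3% against Amphomul lowers it to 73%, 62% or 50%.

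**Reach of the 10% check.** If 30 of the 300 Amphomul patients were drawn at random, which the protocol does not state, P(at least one misread patient is included) = 1 - C(300 - k, 30)/C(300, 30). This is 27%, 47% or 62% for k = 3, 6 or 9 misread patients.

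**The case against.** The case against has real force on five points.

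- **The protocol is silent; it does not say readers are unmasked.** One might infer that microscopists are told the arm or that slides are uncoded. The text does not say so. Section 15.3 names investigators and patients, and the sentence on blinding sits under treatment allocation. What stands is that blinding is declared not applicable for the trial and nothing withholds the arm from the reader.
- **One amastigote does not separate cure from failure at Day 30.** It leads to a repeat aspirate, and a score of 0 at Day 45 is full initial cure. Only at Day 45 does it mean failure.
- **A misread smear does not pass straight into the result.** The patient must also not have cleared by Day 45 and must stay free of relapse to 6 months. The shifts above are therefore ceilings, and nothing in the protocol supports any particular size.
- **There are safeguards.** Magnification, field count and scale are fixed, and slides of 10% of patients are checked independently, so discordance by arm could be examined, though with little precision.
- **The relapse aspirate is not without a role.** A reader might infer that its result counts for nothing in definitive cure. Section 17.2 lists amastigotes on smear as treatment failure, and Section 13 has the 6-month aspirate assess parasitological cure where relapse is indicated. That inference is not supported.

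These points limit the size of the concern. They do not supply the missing instruction.

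**Conclusion.** The point holds as one of exposure. A microscopic reading with a one-object threshold feeds the primary endpoint, is made at the treating centre's laboratory, and is not protected from knowledge of the arm. The 10% check reduces the exposure without removing it. Neither the presence nor the direction of bias can be read from the protocol.

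For scale: at most 1 to 3 points on a 10-point margin if 1% to 3% of Amphomul patients were affected, beside an interval half-width of 4.9 to 8.1 points. The cure rates and the shifts are assumptions.

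This should be changed because the remedy is cheap and the analysis could not reliably undo arm-aware reading afterwards. Masked reading would not cover the clinical suspicion of relapse, which investigators who know the arm will still judge.

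**What to change.** - **Section 19.** State that Day 30, Day 45 and any relapse smears go to the local microscopist and to the quality-control laboratory under a code that does not reveal the arm, and that the score is recorded before it is linked to the patient. The code should differ from the subject ID.
- **Section 15.3.** Replace the statement that blinding does not apply with: *treatment is open-label; smear reading is masked to arm*. Section 15.4, which says code handling does not apply, should be brought into line.

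The definition of definitive cure need not change for this point. Counting a suspected relapse with a negative aspirate as a cure, for example, would alter what the trial estimates.

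Cost: slide labels, short text edits and a few minutes of coding per slide by existing staff. The laboratories, readers and procedures stay the same.
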